## Abstract

**Background:**

Current practice for patients with breast cancer referred for genetic counseling, includes face-to-face consultations with a genetic counselor prior to and following DNA-testing. This is based on guidelines regarding Huntington’s disease in anticipation of high psychosocial impact of DNA-testing for mutations in *BRCA1/2* genes. The initial consultation covers generic information regarding hereditary breast cancer and the (im)possibilities of DNA-testing, prior to such testing. Patients with breast cancer may see this information as irrelevant or unnecessary because individual genetic advice depends on DNA-test results. Also, verbal information is not always remembered well by patients. A different format for this information prior to DNA-testing is possible: replacing initial face-to-face genetic counseling (DNA-intake procedure) by telephone, written and digital information sent to patients’ homes (DNA-direct procedure).

**Methods/design:**

In this intervention study, 150 patients with breast cancer referred to the department of Clinical Genetics of the Radboud University Nijmegen Medical Centre are given the choice between two procedures, DNA-direct (intervention group) or DNA-intake (usual care, control group). During a triage telephone call, patients are excluded if they have problems with Dutch text, family communication, or of psychological or psychiatric nature. Primary outcome measures are satisfaction and psychological distress. Secondary outcome measures are determinants for the participant’s choice of procedure, waiting and processing times, and family characteristics. Data are collected by self-report questionnaires at baseline and following completion of genetic counseling. A minority of participants will receive an invitation for a 30 min semi-structured telephone interview, e.g. confirmed carriers of a *BRCA1/2* mutation, and those who report problems with the procedure.

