### Primary outcomes

#### Choice of procedure

Percentages of patients choosing one procedure over the other (ratio between the two groups) is determined to assess the desirability of the new DNA-direct procedure.

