#### Psychological burden (baseline and follow-up)

##### Quality of Life

To measure global health-related quality of life (QoL), two items scored on a scale of 1-7 were selected from the EORTC-Q30. The full EORTC-Q30 has been widely used and validated for cancer research [47]. The two global QoL items have an excellent internal consistency as proven by the reported Cronbach’s α of 0.91 [48].

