##### General health

The 12-item version of the General Health Questionnaire (GHQ-12) is used as a measure of general psychological distress, using GHQ-scoring of 0,0,1,1 per item (range 0-12) with a threshold of ≥4 to identify ‘caseness', recommended for patients with breast cancer. The GHQ-12 is the shortest version of all GHQs and recommended for research use, with good internal consistency (Cronbach’s α = 0.82 - 0.86) [49-51].

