##### Risk perception

Risk perception of a genetic predisposition for breast cancer, as well as breast cancer recurrence, is measured on a scale of 0-100.

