#### Experiences with genetic counseling (follow-up)

##### Decisional conflict

The difficulty of decision-making, in this study defined as whether or not to undergo genetic testing, is assessed using the traditional format of the Decisional Conflict Scale; 1 item (“I expect to stick to my decision”) is left out as it is not applicable to DNA-testing [57-59]. 15 items scored 0,1,2,3,4 from 0 ‘strongly agree’ to 4 ‘strongly disagree’ remained, including “I am satisfied with my decision” which is also used separately for overall satisfaction. Scores are summed, divided by 15 and multiplied by 25, resulting in a range from 0 to 100. Scores below 25 are considered as ‘no decisional conflict’, between 25 and 37.5 as ‘moderate conflict’ and exceeding 37.5 as ‘severe conflict’. The DCS has good internal consistency exceeding 0.78 [57-59].

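### Abstract and Methods give different primary outcomes, and with eight comparative primary measures and no lead score or margin, mixed results could be reported as acceptable or not

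*Protocol article*

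**What the plan says.** The Methods/design part of the abstract states: "Primary outcome measures are satisfaction and psychological distress". It continues: "Secondary outcome measures are determinants for the participant’s choice of procedure, waiting and processing times, and family characteristics". Choice of procedure is therefore not named as primary there; only its determinants appear, as secondary.

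In the body, the heading Primary outcomes covers nine headed measures before Secondary outcomes begins:

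- **Choice of procedure** comes first: "Percentages of patients choosing one procedure over the other (ratio between the two groups) is determined to assess the desirability".
- The block on **psychological burden**, measured at both time points, holds five: quality of life ("two items scored on a scale of 1-7 were selected from the EORTC-Q30"), the GHQ-12, the Impact of Event Scale (IES), risk perception ("Risk perception of a genetic predisposition for breast cancer, as well as breast cancer recurrence, is measured on a scale of 0-100") and the Cancer Worry Scale.
- The block on **experiences with genetic counseling**, measured at follow-up only, holds three: decisional conflict, satisfaction with choice, and satisfaction with genetic counseling (total 26-104). One decisional conflict item is "which is also used separately for overall satisfaction".

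Statistical analysis sets a single two-tailed level of 0.05 for group comparisons and for a regression of each follow-up result. Sample size calculation gives 80% power, 150 patients and group ratios from 50:50 to 20:80, but ties these to no outcome. The last paragraph of the Background gives the hypothesis: distress no higher than with usual care, satisfaction on a par, and less time spent waiting and processing. It says that this pattern would make DNA-direct acceptable.

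**The concern.** A reader cannot tell from the article which result carries the conclusion. The two lists of primary outcomes differ, and the longer one has eight measures on which the groups will be compared, none of them ranked above the others. The hypothesis is worded as no increase and equality, but the stated tests look for a difference and no margin is given.

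Two opposite reports could therefore follow from the same data. One adverse result among eight could be presented as harm or dismissed as chance. Eight non-significant results could be presented as acceptability even though the study may be too small to exclude a worsening that matters. In both cases the conclusion would depend on which result is emphasised after the data are seen.

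**Working it through.** **1. Compare the lists.** The abstract's two terms correspond broadly to the two Methods blocks, psychological burden to distress and experiences to satisfaction. GHQ-12, IES and cancer worry fit distress. The two satisfaction measures fit satisfaction. Quality of life, risk perception and decisional conflict fit neither term plainly. Choice of procedure fits neither and is the clear discrepancy.

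**2. Count the comparative measures.** There are nine headed measures. Choice of procedure defines the two groups, so it has no between-group test. That leaves 9 − 1 = 8. This counts headings: risk perception has two ratings and satisfaction with choice has several, so the number of tests could be larger, but the article does not fix it.

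**3. Chance of at least one false difference** (one between-group test per measure at 0.05, no true differences).

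- Independent: 1 − 0.95^8 = 0.337.
- Simulated with an assumed common correlation: 0.30 at 0.3, 0.25 at 0.5, 0.19 at 0.7. The article gives no correlations.
- Two independent tests, for comparison: 1 − 0.95^2 = 0.0975.
- False differences against DNA-direct only, eight independent tests: 1 − 0.975^8 = 0.183.

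**4. What 150 patients support.** The figure of 150 cannot be reproduced, because no outcome, effect size, SD or margin is given. Working backwards with the normal approximation for two means, the detectable difference in SD units is (1.960 + 0.842) × √(1/n1 + 1/n2).

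- 75:75 gives 2.802 × 0.1633 = 0.46 SD.
- 30:120 gives 2.802 × 0.2041 = 0.57 SD.

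These apply to one unadjusted comparison. The planned adjustment for confounders is not allowed for.

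**5. If non-significance is read as acceptable.** Take an assumed true worsening of 0.3 SD on one measure. The probability of a non-significant result is Φ(1.960 − 0.3/√(1/n1 + 1/n2)), ignoring the negligible opposite tail.

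- 75:75 gives Φ(1.960 − 1.837) = 0.55.
- 30:120 gives Φ(1.960 − 1.470) = 0.69.

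**6. Joint power if two scores must both succeed.** With 80% each and independence, 0.80 × 0.80 = 0.64. Positive correlation would raise this.

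**The case against.** The strongest reply is that much of this is condensation. An abstract may shorten two blocks of measures to satisfaction and distress, and listing determinants of choice as secondary is compatible with choice itself being primary. That stands for most of the list. It does not explain why the abstract leaves choice of procedure out of the primary outcomes.

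Several stronger readings are tempting, and the document does not support them:

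- **That nine measures are each tested at 0.05.** Choice of procedure has no between-group test, so the number is eight.
- **That there is no rule at all for acceptability.** The Background gives a qualitative rule that joins distress, satisfaction and times. What it lacks is the deciding score and the margin.
- **That 34% is the chance of a false finding of harm.** It assumes independence and counts both directions. The scales come from the same patients and are likely to be correlated, and the adverse direction alone gives about 18%. For a hypothesis of no increase, extra difference tests also make the sought conclusion harder to reach. The missing decision rule therefore matters more than the error rate.
- **That the lack of a multiplicity adjustment is itself a fault.** Such detail is commonly left to an analysis plan, which is not shown. The inconsistent definition of what is primary is visible in the article.

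Two further points are minor. The reuse of one decisional conflict item is openly stated. A two-tailed group comparison of risk perception can be run without a worse direction, although the result would be hard to read as burden.

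**Conclusion.** The concern holds in limited form. The two statements of the primary outcomes disagree, most clearly on choice of procedure. The eight comparative measures under Primary outcomes share one general 0.05 level with no lead score. The criterion for acceptability is qualitative only.

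The chance of at least one false difference is up to about 34%, and roughly 19% to 30% at assumed correlations of 0.7 to 0.3. The larger risk is an undefined conclusion: an assumed worsening of 0.3 SD on one measure would be non-significant with probability about 55% at 50:50 and 69% at 20:80. These figures assume one unadjusted test per measure and normal approximations. The stated 80% power belongs to no identified score.

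The point should be settled before analysis. It does not show that the measures themselves are unsuitable.

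**What to change.** 1. Use the same list of primary outcomes in the abstract and in Methods.
2. Before analysis, name one lead distress score: either the IES for genetic predisposition or the GHQ-12. Both are measured at baseline and follow-up, and the article gives no ground for preferring one.
3. Name one lead satisfaction score, for example the 26-104 counseling total. It is measured at follow-up only, so it cannot be adjusted for its own baseline.
4. State a margin for each, judged by confidence interval. Require both to be met before the distress and satisfaction parts of the Background hypothesis are called supported. Because both must succeed, no split of alpha is needed. Report waiting and processing times alongside, since the hypothesis includes them.
5. Report choice of procedure as a descriptive percentage with a 95% confidence interval.
6. Label the remaining measures secondary.

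**Cost.** Data collection does not change, but this is more than rewording. The sponsor must commit to two scores and two margins, and the documents supply no margin. With a 95% two-sided interval and no true difference, the formula in step 4 of the working also gives the margin that 150 patients support at 80% power: 0.46 SD at 50:50 and 0.57 SD at 20:80. A margin of 0.3 SD would need about 350 or 550 patients respectively. Requiring both scores lowers joint power to about 64% if each has 80% and they are independent. The stated 80% should therefore be tied to a named score or restated.

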**Discussion:**

This study compares current practice of an intake consultation (DNA-intake) to a home informational package of telephone, written and digital information (DNA-direct) prior to DNA-testing in patients with breast cancer. The aim is to determine whether DNA-direct is an acceptable procedure for *BRCA1/2* testing, in order to provide customized care to patients with breast cancer, cutting down on the period of uncertainty during this diagnostic process.

**Trial registration:**

The study is registered at the Dutch Trial Registry http://www.trialregister.nl (NTR3018).

## Background

Patients with breast cancer at high risk of an underlying hereditary predisposition face a time-consuming diagnostic process of several months: it might be helpful to be able to cut down on this long period of uncertainty and provide information applicable to their personal situation as early as possible. Having personal experience with breast cancer, these patients are likely to have enhanced personal risk estimates, thus a higher expectation for protective actions such as longer or more intensive surveillance [1]. Should they carry a pathogenic mutation in either the *BRCA1* or *BRCA2* gene, these patients do have a considerable long term risk for developing a second primary breast cancer (either ipsi- or contralateral) of up to 60% [2-4]. Women recently diagnosed with breast cancer may want to take their *BRCA1/2* status into consideration for their choice of surgical treatment (i.e. breast-conserving with radiotherapy versus ipsi/contralateral mastectomy) and, in the near future, chemotherapy (i.e. PARP-inhibitors) [5-10]. *BRCA1/2* mutation carriers face an additional risk of ovarian cancer ranging from 20-60% for *BRCA1* and 2-20% for *BRCA2*[2-4]. As screening for ovarian cancer through yearly serum CA-125 measurements and transvaginal ultrasound has proven to be ineffective [11-13], clinicians strongly recommend prophylactic bilateral salpingoophorectomy (pBSO) around the age of 35 to 40 years [13]. pBSO reduces the risk of ovarian cancer by 80-90%, and in unaffected premenopausal women simultaneously reduces breast cancer risk by 50% [14,15].

Patients with breast cancer often express concern and uncertainty regarding the risk of breast cancer for their unaffected relatives, especially their sisters and daughters [16]. For unaffected relatives carrying a *BRCA1/2* mutation, cumulative breast cancer risk at the age of 70 years ranges from 40-80% [2-4]. At the age of 25 years, they may choose between an intensive breast cancer screening program consisting of yearly MRI scans, mammography and clinical breast examinations [17,18] or undergoing prophylactic surgery, reducing the risk for breast cancer by 90% [19-21]. Some carriers may still be at an age to be confronted with childbearing conflicts [22]. These are only a few of the life-changing decisions for both patients with breast cancer and their relatives dependent on the results of DNA-testing, which may or may not confirm the presence of a genetic predisposition for breast and ovarian cancer. A previous study in Dutch patients being evaluated for possible breast cancer showed that these patients experienced the period before the final diagnosis as the most stressful, regardless of whether they had received a benign or cancer diagnosis afterwards [23]. This same principle likely applies to *BRCA1/2* testing. Reducing the period of uncertainty in the diagnostic process and offering various forms of information might help substantially.

Another attempt to speed up the diagnostic process concerning hereditary cancer was previously introduced in the evaluation of hereditary colon cancer in the Netherlands. Pathologists are now able to test tumor material of patients younger than 50 years for microsatellite instability (MSI) and immunohistochemical staining of gene products, which may reveal a high a priori risk for an underlying genetic predisposition, without prior consultation of a genetic counselor. If these characteristics are present, patients are referred for further evaluation by a genetic counselor [24,25]. This so-called MIPA procedure (MSI-test by pathologists) is seen by patients as a valuable addition to the diagnostic process of hereditary colon cancer, without feeling either overwhelmed or underinformed, nor showing increased levels of psychosocial distress [26-28].

Such an intervention may also be applicable to patients with breast cancer. As there is no equivalent of tumor material testing in hereditary breast cancer, alternatives for modification must be found within the current diagnostic process. Genetic testing for hereditary breast cancer includes genetic counseling both prior to and following DNA-testing, based on guidelines regarding presymptomatic testing for Huntington’s disease (HD) [29-31]. This approach had been adopted for hereditary breast cancer due to concerns about the psychological consequences of *BRCA1/2* genetic susceptibility testing [32]. However, extensive prior research shows there is no significant long term psychological impact: after an initial increase following *BRCA1/2* testing, psychosocial distress returns to pre-testing levels over time [33-39]. Therefore, in the case of hereditary breast cancer where protective measures are possible, it may not be necessary to adhere to such a strict counseling protocol as defined for an untreatable neurodegenerative disorder such as HD [32]. Patients with breast cancer express the most interest in answers regarding their personal situation: Is my breast cancer of hereditary origin and what are my children’s risks [submitted data by [name]]? Answers to these questions cannot be given until the results of DNA-testing are known. During the initial face-to-face consultation, patients are provided with general information regarding hereditary breast cancer, DNA-testing and possible consequences, prior to actual DNA-testing. Patients consider this generic information less relevant than the personal advice in the second consultation post DNA-testing and may thus experience this intake as an unnecessary delay [40]. It is also widely known that about 40 to 80% of verbal information is immediately forgotten by patients [41]. A recent study in Canada offered a group of Jewish women DNA-testing through written and telephone invitation. The majority of these women had positive experiences with this approach and considered it to be effective [42]. Providing patients with alternative means to educate themselves regarding hereditary breast cancer and DNA-testing, prior to their decision to undergo testing, might improve patient recollection of medical information as well as increase patient participation.

Therefore, this study offers patients with breast cancer the choice of replacing the initial face-to-face consultation prior to DNA-testing (usual care DNA-intake procedure) by a home information package including telephone, written and digital information consisting of a website and educational movie (DNA-direct procedure). DNA-testing will thus be performed prior to genetic counseling, contrary to current practice. At the first face-to-face contact, counselors will be able to disclose DNA-results and customized advice to patients. This eliminates extraneous information which is not applicable to the individual patient, and provides patients with the information they desire in a quick and patient-centric manner.

The aim of this intervention study is to compare this new DNA-direct procedure to current practice (DNA-intake procedure). The effects of the DNA-direct procedure on the experience and psychosocial distress on patients with breast cancer, as well as the speed and quality of genetic advice, will be evaluated. The hypothesis is that undergoing the DNA-direct procedure does not lead to increased levels of psychosocial distress as compared to the usual care DNA-intake procedure, with equal levels of patient satisfaction plus shorter waiting and processing times. A trend similar to traditional *BRCA1/2* testing – a short term increase in distress, falling back to pre-testing levels over time [33-39] – is expected in the DNA-direct procedure. This would make DNA-direct an acceptable procedure for patients with breast cancer undergoing genetic testing, with the goal of more customized care, and a shorter period of uncertainty. Moreover, it would facilitate taking genetic advice into account for the treatment and follow-up of breast cancer.

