## Methods/design

### Design

The study examines the effect of the DNA-direct procedure on the experience and psychological distress of patients with breast cancer as well as several secondary outcome measures, including waiting and processing times, as compared to the current DNA-intake procedure. Two groups will be compared: the intervention group, who choose to undergo the DNA-direct procedure, and the control group, who will receive care as usual (DNA-intake procedure). Participants may choose freely between the DNA-direct versus DNA-intake procedures. This study is not randomized due to the wish to evaluate whether there is indeed a desire for the proposed DNA-direct procedure amongst patients with breast cancer, and to evaluate the reasons stated for preferring one procedure over the other.

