## Discussion

Considering today’s call for more patient participation in medical decision-making, the convenience of taking up information and drawing blood close to home, paired with customized advice from the very first consultation, might appeal to patients. Replacing the face-to-face intake consultation with a genetic counselor by a home informational package of telephone, written and digital information might speed up the diagnostic process of hereditary breast cancer and reduce extraneous information. For example, this would allow patients to go over this information at their own convenience and in their own homes. It could possibly reduce travel efforts to a hospital as well as time conflicts with breast cancer therapy.

However, there are certain downsides compared to traditional genetic testing. All patients with breast cancer referred to clinical genetics by their treating physician are eligible for the DNA-direct procedure. This means that even those patients who would not normally fulfill criteria for *BRCA1/2* testing are now able to have their blood drawn for DNA-testing, regardless of those criteria. In the DNA-intake procedure, patients who do not fulfill the aforementioned criteria will not be offered further DNA-testing. This may lead to a selection bias. Our intention is to compare DNA-direct to current practice: adhering to these criteria is the current practice and must be reflected in the DNA-intake procedure.

Additionally, genetic counselors must adjust their counseling styles to the disclosure of the DNA-results being the first order of business, without having built up a counselor-patient relationship beforehand. New information might come forward following result disclosure, leading to ad-hoc modification of screening advice. For this reason, as well as to avoid intercounselor variation, we have selected five genetic counselors with many years of experience in oncogenetic counseling to see all patients participating in this study (both DNA-direct and DNA-intake).

In conclusion, the aim of our study is to determine whether DNA-direct is an acceptable procedure for *BRCA1/2* testing, in order to provide customized care to patients with breast cancer and remove unnecessary waiting times within the diagnostic process, cutting down on the long period of uncertainty that patients are currently faced with.

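### The aim and hypothesis claim an effect of DNA-direct against usual care, but the study compares women who chose DNA-direct with women who declined it

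*Protocol article*

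**What the plan says.** The Background of the protocol article gives the aim as "The aim of this intervention study is to compare this new DNA-direct procedure to current practice (DNA-intake procedure"). Its hypothesis is that DNA-direct "does not lead to increased levels of psychosocial distress as compared to the usual care DNA-intake procedure", with satisfaction equal and times shorter. The Design section likewise describes the study as examining the effect of DNA-direct relative to the current intake procedure.

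The groups are formed as follows. Under Design, "Participants may choose freely between the DNA-direct versus DNA-intake procedures", and the two groups are "the intervention group, who choose to undergo the DNA-direct procedure, and the control group, who will receive care as usual (DNA-intake procedure"). Under Recruitment, both procedures are explained in the telephone call that also checks the exclusion criteria. Women who fail triage go to a regular intake consultation, but by the Study sample section they are excluded from the study.

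The Statistical analysis section plans a regression of follow-up results on group, with baseline results as covariates plus variables that were significant in univariate tests.

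**The concern.** A claim about the effect of replacing the intake consultation needs to know how the same kind of woman would have fared with the intake. The control group cannot show this, because women who wanted DNA-direct have left it.

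The article itself gives a reason to expect the two kinds of women to differ. It argues that patients "may thus experience this intake as an unnecessary delay", and women of that view could be expected to take DNA-direct.

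What is at stake is how a null result is read. If distress and satisfaction turn out similar, the hypothesis as worded would be reported as confirmed: no added distress and equal satisfaction against usual care. The data would show only that two groups of women, each given the procedure she picked, reported similar outcomes.

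**Working it through.** **Claim and contrast side by side.**
- Comparator named in the aim and hypothesis: current practice or usual care, meaning the DNA-intake procedure (Background, Design).
- Control group observed: women offered both procedures who took intake (Design, Recruitment).
- Any other intake group: none. There is no randomized group and no group seen without the offer. Triaged-out women attend intake but are not participants.

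**What the contrast estimates.** Write pd for women who prefer DNA-direct and pi for women who prefer intake. Let D and I be mean follow-up outcomes under DNA-direct and intake.

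- Observed, before adjustment: D(pd) − I(pi).
- Add and subtract I(pd): [D(pd) − I(pd)] + [I(pd) − I(pi)] = t + g.
- t is the effect of replacing intake in women who would choose DNA-direct, the patients whose care the new option changes. g is the gap, under the same intake procedure, between the two kinds of women.
- I(pd) is never observed, so t and g cannot be separated. The share choosing DNA-direct does not enter, so the bias is g at 50:50 and equally at 20:80.

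**What regression can do.**
- Quality of life, GHQ-12, the Impact of Event Scale for genetic predisposition, risk perception and the Cancer Worry Scale are taken at baseline and follow-up. Baseline adjustment can remove the part of g carried by these scores.
- Information need and empowerment, also taken at baseline, may remove a little more if they enter the model.
- Decisional conflict, satisfaction with choice and satisfaction with counselling are collected at follow-up only, so there is no baseline value of the outcome to adjust for.
- Preference takes one value in each group. It is collinear with the group term and cannot be a covariate.

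**Scale.** The total of 150 (80% power, two-sided 0.05, ratios from 50:50 to 20:80) cannot be reproduced, because no effect size, SD or margin is given. Solved backwards for an unadjusted comparison of two means, the detectable difference is (1.960 + 0.842) × √(1/n₁ + 1/n₂):
- 75 and 75: 2.802 × 0.1633 = 0.457 SD
- 30 and 120: 2.802 × 0.2041 = 0.572 SD

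A larger sample would narrow the interval around t + g; it would not remove g.

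The documents give no g, so the values below are assumptions. With t = 0, the approximate probability of a significant difference in the direction of g is Φ(g/SE − 1.960), with SE = 0.1633 or 0.2041 SD:

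| Assumed g (SD) | 75 and 75 | 30 and 120 |
|---|---|---|
| 0.2 | 0.23 | 0.16 |
| 0.3 | 0.45 | 0.31 |
| 0.5 | 0.87 | 0.69 |

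In the other direction, if a true harm of 0.5 SD met a favourable gap of 0.3 SD, the apparent difference would be 0.2 SD. Power would then fall from 0.87 to 0.23 (75 and 75) or from 0.69 to 0.16 (30 and 120). So g can create a difference or hide one. These are unadjusted figures; baseline adjustment would shrink g by an unknown amount for the distress scales.

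**The case against.** **The design is disclosed.** This stands. The Background says that patients are offered a choice. Design says the study is not randomized and gives the reason: to learn whether DNA-direct is wanted and why. Choice of procedure heads the primary outcomes, and the Sample size calculation section admits confounders that are not all known. A reader might infer that the choice is concealed or that the trial ought to have been randomized; neither follows. But the stated reason supports a study of preference. It does not support a claim of no added distress or equal satisfaction caused by replacing intake.

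**Current practice may mean only the intake procedure.** The abstract says "Current practice for patients with breast cancer referred for genetic counseling, includes face-to-face consultations with a genetic counselor prior to and following DNA-testing" and mentions no alternative, so a reader might take the comparator to be intake for every patient with no choice. The aim, however, glosses current practice as the DNA-intake procedure, so the narrower reading is open. The point survives it, because I(pd) is unobserved either way.

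**The direction of bias is not known.** This also stands. A reader might infer that giving each woman her preferred procedure must pull the groups toward equality, or that controls must look more satisfied than under usual care. The remark about unnecessary delay concerns patients in general and is worded as a possibility. It says nothing about how either kind of woman would rate the intake.

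**The Discussion makes no equality claim.** Correct. Its sentence "Our intention is to compare DNA-direct to current practice" introduces a point about criteria for BRCA1/2 testing, not about patient choice. The Discussion and the abstract's discussion ask whether DNA-direct is acceptable for customized care, which is already close to what the study can show.

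**Conclusion.** The point holds as a mismatch between the claim and the contrast measured. Background and Design promise an effect against usual care; the study delivers a comparison between women who chose DNA-direct and women who declined it.

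Against intake outcomes in women who prefer DNA-direct, the unadjusted bias equals g at any choice ratio. Its size and sign cannot be derived from the documents, and the tabulated probabilities rest wholly on assumed values of g. Adjustment may reduce the bias for distress. For satisfaction and decisional conflict it has less to work with.

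The proportion choosing DNA-direct and the reasons for the choice are unaffected, since they are what a choice design measures well. The correction is worth making because it changes what a null result may be said to show.

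**What to change.** 1. In the Background (aim and hypothesis) and in Design, restate the comparison as: women who chose DNA-direct versus women who chose DNA-intake when both were offered. Do not conclude that replacing intake under current practice leaves satisfaction equal or distress no higher.
2. In the abstract's discussion, the Background and the Discussion, limit the conclusion to DNA-direct being acceptable as an option for women who choose it.
3. In the Discussion, name choice of procedure as a source of selection bias beside the testing-criteria bias already given there. Say that the regression addresses measured baseline differences only.

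The cost is a narrower claim. No extra participants, data or analyses are needed, and the sample size and primary outcomes stay as they are.
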